**Figure 4 Fig4:**
[figure not shown]
**GermanIMPACT study design.**

### Ethical considerations and safety

#### Good clinical practice

The collaborative care model used in this study has proven beneficial in numerous trials. The treatment plan and intervention techniques are compliant with recommendations of current national and international clinical guidelines. GermanIMPACT follows the regulations of the Federal and State Data Protection Law and the recommendations of the Harmonized Tripartite Guideline for Good Clinical Practice (ICH GCP). All relevant protocol modifications and amendments will be submitted to the responsible ethical review boards and will be reported within the scope of the publication of the trial findings.

Patients with severe depressive symptoms or suicidal ideation at the time of screening are excluded from study participation. GPs are encouraged to refer these patients to an external MHS. Severe depressive symptoms or warning signs of suicide that occur during the intervention can be detected early and be dealt with in a timely manner. In case of adverse advents, such as the emergence of warning signs of suicide in the course of the intervention, the responsible GP and MHS must be consulted instantly by the CM and decide on further action. Different options are possible: 1) GP and MHS can consult to discuss further action; 2) the MHS can make a personal appointment with the patient; or 3) the MHS or GP can initiate further steps, for instance, hospitalization. For patients in the control group, the data management team monitors the development of the depressive symptoms by screening the incoming questionnaires for suicidal cues. A SOP for screening and step-by-step instructions are provided, namely, requesting the patient to see their GP as soon as possible, to make an appointment with a psychiatrist or psychotherapist, or, in case of an emergency, to call emergency medical services directly. The GP and the MHS can then decide about further steps for medical care. All adverse events that occur during the trial will be documented by the CM or, for patients in the control group, by the data management team. Study participation does not exclude the option of referral to an external specialist, although for patients in the intervention group, GPs are encouraged to refer them to the supervising MHS. Thus, both patient groups have full access to all treatment options for depression in the German healthcare system. As treatment by the GP is maintained during and after the trial phase, no post-trial care is intended, and the GP can decide about additional treatment options as needed.

The trial protocol has been granted ethical approval from the ethical review board of the University of Freiburg (approval number 150/12) and the ethical review board of the medical association of Hamburg (approval number MC-224/12). Written informed consent is mandatory for each patient for enrollment in the study.

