#### Care manager-patient contact

In a 60-minute face-to-face session, the CM provides a short overview of the 12-month treatment period and introduces the patient to the basic intervention techniques and the patient workbook. A semi-structured interview serves to assess the patient’s current health status and behavior, symptoms, medication, and psychosocial stressors and resources; the answers serve as a starting point for the individual intervention plan. As a first task, the patient is encouraged to keep an activity journal for the next seven days.

One week later, the initial session is followed by a 60-minute telephone session during which behavioral activation is revisited and patients are sensitized to the positive relationship between activity and mood improvement. With the help of the activity journal, a list of pleasant activities is created from which the patient is encouraged to choose two and to integrate them into their daily routine. After this second session, 30-minute telephone sessions are held every other week. Every session consists of a short symptom assessment via the PHQ-9 and a short interview including questions about GP visits, medication effects and adherence, and experiences with the behavioral activation tasks. Potential barriers for activity planning and realization are carefully analyzed and new tasks for the next 14-day period are selected accordingly. Due to the regular contact between the CM and patient, the CM can monitor and record deviances from the planned intervention and react instantly to difficulties regarding adherence to the protocol.

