**Table 1 Tab1:** **GermanIMPACT stepped-care algorithm**

Change of current PHQ score compared to baseline	Recommended step
**Improvement of less than 50%** (including no improvement and worsening of symptoms)	a) Medication-related changes (initiated by the GP) including initiation if patient is currently without medication, or
	b) Training of problem-solving techniques provided by the care manager: two face-to-face sessions, four telephone sessions (approximately 45 minutes each); afterwards resumption of telephone sessions at two-week intervals
**Improvement of 50% or more**	No treatment changes
**PHQ-9 score <5** (remission)	c) Discussion of a relapse prevention and emergency plan
	d) Reduction of telephone sessions to four-week intervals; in case of relapse, resumption of telephone sessions at two-week intervals

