As after assignment the research stuff is not blinded, no external data monitoring committee is needed, and data concerning patient safety and treatment efficacy can be monitored internally. Similarly, auditing of the trial conduct will be administered by the research staff: the data management teams in Freiburg and Hamburg will monitor the completion of the questionnaires, while the study coordinators will ensure adherence to the intervention protocol.

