#### Dissemination

The trial is registered in the German Clinical Trials Registry (DRKS-ID: DRKS0000358). The results of the trial will be published in international academic journals and national periodicals for healthcare professionals and will be disseminated through presentations at scientific conferences. Participating GPs will receive the publication of the main analyses and additional information in lay language to disseminate them to interested patients. The sponsor will receive a final report including recommendations on development requirements of collaborative care in late-life depression therapy in primary care - according to the results of the trial. There is no restriction on publication. The trial is conducted according to the CONSORT statement, and the study protocol conforms to the Spirit Checklist [48]. The use of professional writers is not intended. So far, no public access to full protocol, participant-level dataset, and statistical code is planned.

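### Adverse events are documented through different routes in the two arms, and suicidal-cue screening of the follow-up forms is assigned only for controls, so any by-arm safety comparison would have unequal ascertainment

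*Protocol article*

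**What the plan says.** Four parts of the protocol article bear on this.

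- **Who records and who screens (Ethical considerations and safety).** Adverse events are "documented by the CM or, for patients in the control group, by the data management team". On suicidality: "For patients in the control group, the data management team monitors the development of the depressive symptoms by screening the incoming questionnaires for suicidal cues". The article mentions, but does not show, a standard operating procedure for that screen. In the intervention arm the CM brings in the GP and the mental health specialist when warning signs emerge.
- **Intervention-arm contacts (Care manager-patient contact; Table 1).** There is a face-to-face session and a telephone session one week later. The schedule then continues: "After this second session, 30-minute telephone sessions are held every other week". The CM administers a PHQ-9 at each of these contacts. On remission, Table 1 recommends: "Reduction of telephone sessions to four-week intervals".
- **Forms common to both arms (Blinding; Assessment; Table 2).** Both arms receive the same mailed PHQ-9 at baseline, 6 and 12 months. The data management team collects outcomes in both arms, so that the CM is kept out of assessment. Patients with missing forms are telephoned every 10 to 14 days, and those who discontinue or deviate from the intervention get a final telephone survey.
- **Oversight (monitoring paragraph after Table 2).** There is no external committee; "data concerning patient safety and treatment efficacy can be monitored internally".

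**The concern.** The source of safety information, the person who records it and the frequency of asking all differ by arm. In the intervention arm the recorder also delivers the treatment. A count of adverse events or suicidal cues set side by side by arm would mix the true rates with the number of opportunities to notice an event. A real harm could not be told from closer observation, and a real benefit could be hidden by it.

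There is also a gap in coverage as written. The follow-up forms go to the data management team, not to the CM, and the team's suicidal-cue screen is assigned only for control patients. Two kinds of intervention-arm form then have no assigned screen and no CM session behind them: forms from patients who have stopped CM contact, and month-12 forms returned after the last session. Table 2 places the month-12 assessment after the intervention, and reminder calls can push its return later still.

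**Working it through.** The article gives no figure for safety detection, so there is none to reproduce. The contacts can be counted from its schedules.

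**Scheduled contacts over 52 weeks**

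- Intervention arm, no step-down: week 0, week 1, then weeks 3, 5, ..., 51. That is 1 + 1 + 25 = 27.
- Intervention arm, remission at the first eight-week evaluation: weeks 0, 1, 3, 5, 7, 9, then 13, 17, ..., 49, so 6 + 10 = 16. If the evaluation is a separate week-8 session followed by weeks 12, 16, ..., 52, the count is 6 + 11 = 17.
- Control arm: mailed forms at months 6 and 12, so 2.
- Ratio: 16/2 = 8 to 27/2 = 13.5.

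The problem-solving sessions in Table 1 are left out because their spacing is not given. Reminder calls and the final telephone survey are left out because neither is described as a safety check.

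**What the difference could do to a count**

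Assumptions, none from the documents: onset is uniform over 52 weeks, a cue lasts d weeks and is recalled for 2 weeks more, and every contact or form is completed. A cue is caught if a scheduled contact falls within d + 2 weeks of onset.

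- Control forms at weeks 26 and 52: probability = 2(d + 2)/52.
- Fortnightly CM contacts, last at week 51: every gap is covered, so 51/52 = 0.98.
- CM contacts with step-down, last at week 49: for d of 2 or more every gap is covered, so 49/52 = 0.94.

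| Cue duration d (weeks) | CM, fortnightly | CM, step-down | Control forms |
|---|---|---|---|
| 2 | 0.98 | 0.94 | 8/52 = 0.15 |
| 4 | 0.98 | 0.94 | 12/52 = 0.23 |
| 8 | 0.98 | 0.94 | 20/52 = 0.38 |
| 12 | 0.98 | 0.94 | 28/52 = 0.54 |

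At the other extreme, an event recalled over the full six months (26 weeks) is covered by the control forms with probability 2 × 26/52 = 1.00. The difference then all but disappears.

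**The screening assignment**

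The article's other statement on reviewing forms is under Recruitment of patients: completed questionnaires are checked against the exclusion criteria, which include suicidal ideation, without restriction by arm. That sentence follows the sending of the baseline questionnaire and concerns eligibility, so it does not settle months 6 and 12. For those forms the suicidal-cue screen is named for one arm and neither assigned nor ruled out for the other.

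**The case against.** The strongest case on the other side has five parts.

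- **The text does not say that intervention patients' forms go unscreened.** A reader might infer this from the control-only wording, but the article does not state it. The screening procedure is not shown, the same team handles both arms' forms, and all team members are instructed in dealing with suicidal ideation. This stands: the supportable statement is that the screen is unassigned for these forms. What remains is that the article states an arm-specific rule, which is more than an omission of detail.
- **No by-arm safety comparison is planned.** Safety is not among the listed outcomes, and Statistical analysis contains no adverse-event comparison. A reader might infer one from "The trial is conducted according to the CONSORT statement", but the document does not say what that entails for safety reporting. This stands: the bias concerns a comparison if one is made.
- **Some safety-relevant data are collected alike.** It would be wrong to say that nothing is. The mailed PHQ-9 is identical in both arms and handled by the same team; it is only not designated as the common safety source. This stands, and it makes the fix easy.
- **Two forms may not be the only control-arm source.** The article does not say where control-arm adverse events come from; it ties the forms only to the suicidal-cue screen. Reminder calls and the final telephone survey add contacts. This stands in part: the ratio compares scheduled contacts, not all possible routes.
- **Closer contact is the intervention itself.** Some asymmetry is inherent and is not a fault. The primary PHQ-9 outcome comes from the mailed forms, so this asymmetry does not reach it.

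**Conclusion.** The point holds in limited form. Adverse-event documentation follows a different route in each arm, with about 16 to 27 scheduled CM contacts against 2 scheduled follow-up forms. Suicidal-cue screening of the month-6 and month-12 forms is assigned only for controls. Any by-arm comparison of adverse events or suicidal cues would have unequal ascertainment, tending to inflate the intervention arm's count.

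The size cannot be fixed from the documents. It is large for short-lived cues with short recall and small for events recalled over six months. The contact counts assume that all scheduled sessions and forms are completed. The point is worth correcting because suicidality is the safety event that the protocol itself singles out, safety monitoring is internal, and the remedy uses forms already collected.

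**What to change.** - State that the existing questionnaire-screening procedure applies to the month-6 and month-12 forms of both arms.
- State that any by-arm safety comparison uses only this common source, namely the suicidality item of the mailed PHQ-9.
- Report events found only through CM sessions separately, as intervention-arm data not compared with control. Keep them fully available to internal safety monitoring; the restriction is on comparison only.
- Leave the response to a positive screen to the existing procedures.

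The cost is a sentence in the safety section and one reporting rule. The same team already receives the forms of both arms, so the extra screening is slight. The by-arm comparison will contain fewer events. Table 2 lists no adverse-event instrument, so other adverse events would stay outside that comparison unless the forms ask about them in both arms.

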### Training of GermanIMPACT care providers

The CMs receive comprehensive training by a psychologist familiar with the IMPACT concept and intervention techniques. They are provided with a detailed intervention manual to be used for further study and reference. Regular meetings with the trainers ensure the continuous high standard of the intervention. Clinical concerns are regularly discussed with the supervising MHS. All members of the GermanIMPACT study team are educated and instructed thoroughly in how to deal with emergencies, such as suicidal ideation.

Prior to participation, GPs are individually contacted by members of the study team and informed about the aims of the study and the nature and process of the intervention. Before the inclusion of the first patient, they are personally introduced to the CM assigned to their office.

### Data protection

All patient data collected throughout the study, including documentation of the intervention sessions, are entered into the study database using identifiers (pseudonyms) instead of patient names to grant the highest possible protection of privacy. The necessary exchange of patient data between the providers within the treatment triad is clearly communicated orally, in the patient information and the informed consent form. Health-related and sociodemographic data will be stored separately from personal data. Only authorized staff has access to the data, and data privacy protection according to German Law will be fulfilled. All institutions cooperating in the study are required to agree to the data protection procedures. All investigators will have access to the final trial dataset without any contractual limitations.

#### Dissemination

The trial is registered in the German Clinical Trials Registry (DRKS-ID: DRKS0000358). The results of the trial will be published in international academic journals and national periodicals for healthcare professionals and will be disseminated through presentations at scientific conferences. Participating GPs will receive the publication of the main analyses and additional information in lay language to disseminate them to interested patients. The sponsor will receive a final report including recommendations on development requirements of collaborative care in late-life depression therapy in primary care - according to the results of the trial. There is no restriction on publication. The trial is conducted according to the CONSORT statement, and the study protocol conforms to the Spirit Checklist [48]. The use of professional writers is not intended. So far, no public access to full protocol, participant-level dataset, and statistical code is planned.

## Discussion

The IMPACT approach to treat late-life depression has proven both effective and cost-effective in the United States for more than a decade. Not surprisingly, collaborative models are increasingly recognized in international research on depression care. The adapted GermanIMPACT program is tailored to the specific primary care context in Germany, for instance, with regard to GP medical practice, office organization, infrastructure, communication style, and patient characteristics. By preserving the core principles of the original program, we expect that our collaborative intervention will show effects that are as beneficial as those of its American counterpart.

In the face of the demographic transition and the high prevalence rates of clinically relevant depressive symptoms in the older age groups, collaborative interventions for older adults are a forward-looking approach [2]. We expect that older adults can benefit greatly from a low-threshold intervention like GermanIMPACT that supports, but does not replace the usual treatment by their long-standing family doctor. We hope that the results from our study will help to identify and understand impeding and facilitating factors to the process of integrating CMs into a patient’s treatment plan. Since the notion of collaborative depression care is fairly new to the German healthcare system, we hope that the results of the GermanIMPACT study will yield important insights regarding the applicability of collaborative models and pave the way for the implementation of CMs into outpatient depression treatment in Germany.

## Trial status

Enrollment for the trial began in February 2013. Recruitment is still in progress. Data collection is expected to continue until September 2015.

## Abbreviations

CDC: Collaborative depression care
CDI: the Comorbidity Disease Index
CG: Control Group
CM: Care manager
CPG: the Graded Chronic Pain Scale
EM: expectation-maximization
EQ-5D: EuroQol Group
FIMA: Fragebogen zur Inanspruchnahme medizinischer und nicht-medizinischer Versorgungsleistungen im Alter
GAD-7: the Generalized Anxiety Disorder seven-Item Scale
GCP: Good Clinical Practice
GP: General practitioner
ICD-10: International Classification of Diseases
ICH: International Conference on Harmonization
IG: Intervention Group
IMPACT: Improving Mood Promoting Access to Collaborative Treatment
MHS: Mental health specialist
PHQ-9: the Patient Health Questionnaire
PST: Problem-solving techniques
RS-13: the 13-item Resilience Scale
SAP: Statistical analysis plan
SOP: Standard operation procedure.
